## Abstract

**Background:**

Hospital malnutrition is an underestimated problem and as many as half of malnourished patients do not receive appropriate treatment. In order to extend the management of malnutrition in health care facilities, multidisciplinary teams focusing on clinical nutrition were established in France. The establishment of such teams within hospital facilities remains nonetheless difficult. We have consequently developed a multifaceted intervention coordinated by a Nutritional Support Team (NST). Our study aims to evaluate the impact of this multifaceted intervention coordinated by a NST, in adherence to recommended practices for the care of malnourished children, among health care workers of a paediatric university hospital.

**Methods/design:**

We carried out 1) a six-month observational phase focusing on the medical care procedures relative to malnourished children followed by 2) a cluster randomised controlled trial phase to evaluate the impact of a multidisciplinary nutrition team over an 18 month time frame.

Based on power analyses and assuming a conservative intracluster correlation coefficient, 1289 children were needed to detect a 25% difference in rates between the two groups of the cluster trial.

The implementation of our intervention was coordinated by the NST and had three major components: a) access to a computerised malnutrition screening system associated with an automatic alert system, b) an awareness campaign directed toward the health care workers and c) a leadership based strategy.

Main outcomes included the number of daily weighings during hospitalisation, the investigation of malnutrition etiology and the management of malnutrition by a dietician and/or the NST.

Due to the clustered nature of the data with children nested in departments, a generalized estimated equations approach will be used to analyse the impact of the multifaceted intervention on primary and secondary outcomes.

**Discussion:**

Our results will provide an overall response regarding the effectiveness of our multifaceted intervention and we should be able to suggest an organization and mode of operation of NST.

**Trial registration:**

ClinicalTrials.gov: NCT01081587.

## Background

The problem of hospital malnutrition has been identified only over the last thirty years or so. It is an issue that occurs frequently, with 15 to 30% of hospitalised children in industrialised nations qualifying as malnourished [1-3] and with nearly 50% at risk for malnutrition during their hospital stay [4]. Because it increases morbidity and mortality risk for the subjects affected (through issues such as infections, metabolic disorders, pressure ulcers and postoperative complications), malnutrition is potentially serious [5].

Hospital malnutrition is an underestimated problem. As many as half of malnourished children do not receive appropriate treatment for this issue, even in university hospital centres [6,7]. One of the main obstacles to the provision of quality care to malnourished children is their dispersal among a hospital’s various medical departments [8]. In addition, this care requires the coordinated involvement of physicians, dieticians, nurses, paediatric auxiliary nurses and physiotherapists.

The Committee on Nutrition of the European Society for Paediatric Gastroenterology, Hepatology and Nutrition (ESPGHAN) has issued recommendations to establish nutrition support teams in paediatric hospitals, to implement screening for nutritional risk, to identify patients who require nutritional support, to provide adequate nutritional management, to educate and train hospital staff, and to audit practice [9]. In order to extend the management of malnutrition in health care facilities, multidisciplinary teams focusing on clinical nutrition were established on an experimental basis in France starting in 2007 [10]. These multidisciplinary nutrition teams comprise physician nutrition specialists, nurses and dieticians. Such forms of organisation should facilitate the treatment of malnutrition in hospitals, involving clinical teams in systematic nutritional assessment that enables screening and leads to appropriate treatment [11]. The introduction of such teams should make it possible to reduce the prevalence of complications linked to malnutrition, improve the prescription of nutritional supplements and promote the dissemination of good practice, thereby leading to substantial economic savings [11].

The establishment of such teams within hospital facilities remains nonetheless difficult. In addition, the Nutritional Support Team (NST) is not always addressed appropriately, and an intervention strategy is required. We have consequently developed a multifaceted intervention that was coordinated by the NST and that aimed to:

– Raise awareness regarding the malnutrition issue,

– Train clinical teams regarding guidelines for good practice,

– Facilitate the screening of malnourished children through the use of an electronic alert system,

– Assist in decision making regarding the clinical teams’ care and treatment of malnourished children, with either a dietician or the NST enlisted to provide expertise,

– Coordinate nutritional care among several categories of health care professionals (nurses, auxiliaries, physicians and dieticians).

French guidelines for good practice relative to hospital malnutrition refer to a nutritional care algorithm that uses the children’s weight/height and height/age ratios [12]. The integration of this algorithm, as an automated decision support tool within the hospital data processing system, should improve the relevance of the multidisciplinary nutrition team’s interventions on hospitalised malnourished children [13].

This study aims to evaluate the impact of a multifaceted intervention (including electronic medical alerts) coordinated by a NST, in compliance with to recommended practices for the care of malnourished children, among health care workers of a paediatric university hospital.

## Methods/design

### Study design

Within a paediatric university hospital, we carried out 1) a six-month observational phase focusing on the medical care procedures relative to malnourished children followed by 2) a cluster randomised controlled trial phase to evaluate the impact of a multidisciplinary nutrition team over an 18 month time frame. This cluster randomised design was chosen because the multifaceted intervention was conducted at the practice level and outcomes were measured at the patient level.

### Participants

Our inclusion and exclusion criteria, at both cluster and patient levels, are presented in Table 1.

**Table 1 T1:** Inclusion and exclusion criteria

**Population at cluster level**	
***Study units***	
*Inclusion criteria*	Medical and surgical units in a teaching hospital providing paediatric acute care
*Exclusion criteria*	Neonatal care units, intensive care units and emergency units
***Health care workers***	
*Inclusion criteria*	Any hospital staff involved in direct patient care (includes physicians, nurses, nursing assistants, physiotherapists and dieticians)
**Population at patient level**	
*Inclusion criteria*	Age 1 month to 18 years old
	Children recorded as malnourished based on their weight/height and height/age ratios upon hospital entrance, according to the Algoped nutritional risk score
*Exclusion criteria*	Age under one month, liver or kidney abnormalities, severe heart failure
	First weight recorded more than 2 days after admission, first height recorded more than 15 days after admission
	Stay less than 2 days

Head physicians of all eligible departments were contacted and invited to participate. All medical and surgical departments providing acute care in this paediatric university hospital participated in the trial (*i.e.*, 8 departments, 393 acute care beds (207 in medicine and 59 in surgery) performing 29 518 stays a year) except neonatal, intensive care and emergency units. Approximately 300 professionals were targeted (55 physicians and medical residents, 115 nurses, 12 dieticians, 100 paediatric auxiliary nurses and 27 physiotherapists).

Some nursing teams work across several departments. As a consequence, because our intervention targeted the practices of health care professionals, we grouped the relevant departments together into clusters in order to minimise contamination bias between departments. A total of six clusters were determined.

According to the French paediatric guidelines for the screening and treatment of malnutrition, the Algoped nutritional risk score was employed for assessing the nutritional status of every child based on weight and height measured at admission by health care workers [11]. Detection of malnourished children was based on the combined interpretation of two ratios. First, in order to detect acute malnutrition (stunting), the weight/height ratio (W/H) was calculated by dividing the child’s observed weight by the expected weight related to their observed height [14]. Second, in order to detect chronic malnutrition (wasting), the height/age ratio (H/A) was calculated by dividing the child’s observed height by the expected height related to their age. In cases of W/H > 90% and/or H/A > 94%, there was considered to be no malnutrition in the patient. In cases of W/H 80-90% and/or H/A 85-94%, there was moderate malnutrition, while W/H < 80% and/or H/A < 85% indicated severe malnutrition [15,16].

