#### Leadership based strategy

A leadership oriented strategy focused mainly on increasing the sensitivity of the computerised malnutrition screening system. To this end, the medical and nursing advisory boards of the hospital established the mandatory measurement of the weight and height of each hospitalised child, as well as the mandatory entry of these data into the IT system. In terms of intervention, the medical heads and nursing coordinators of each department were in charge of ensuring compliance with this recommendation. In addition, the NST was responsible for coordinating the dieticians across the hospital and for leading a periodic multidisciplinary meeting in order to analyse clinical incidents related to nutritional care and to facilitate the sharing of experience among attendees from various medical specialties.

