### The control group

In the control arm, no specific intervention was implemented to improve the management of malnutrition (*i.e.*, with no access to the computerised malnutrition screening system, no educational campaign and no leadership based strategy) and the teams provided care as usual. In addition, as usual, the NST could be called for counselling at any time within the control arm.

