### Data analysis of the cluster randomised trial

All statistical analyses will be performed in Statistical Analysis System (SAS®) software version 9.2 (SAS Institute, Cary, NC). Analyses will be performed according to the intention-to-treat principle. All malnourished children screened in all clusters allocated to the intervention or control arm will be included in the analysis. In the event of multiple hospitalisations for the same patient, only the first stay of the study period will be retained.

Baseline characteristics will be summarised by pre- and post-intervention period and treatment group using frequency (percentage) for categorical variables and means (standard deviation) for continuous variables.

Clustering will be taken into account: a generalized estimated equations (GEE) approach will be used to analyse the impact of the multifaceted intervention on primary and secondary outcomes [20]. A GEE Poisson regression model will be performed for count data (as number of daily weighings) and GEE logistic regression models for binary variables (as investigation of malnutrition etiology, management by dietician, nutritional supplementation, complication occurrence during hospitalisation). The paediatric departments will be entered as the clustering variable into each model. For the GEE Poisson, the length of stay will be used as an offset. An exchangeable correlation matrix will be specified to account for potential within-cluster homogeneity in outcomes: all pairwise correlations among children within departments are the same. Robust estimates of the standard errors will be obtained which ensures, provided the model is correct, that the estimates are consistent even if the working correlation matrix is not correct. The impact of the multifaceted intervention will be adjusted for individual level characteristics included age, severity of malnutrition, comorbidities occurrence, complications occurrence and length of hospital stay after controlling for the collinearity between covariables. A Wald statistic will be used to test the significance of each coefficient in the model. The intervention effect will be expressed as adjusted odds ratio with its 95% confidence interval. GEE regression models will be fit using the SAS PROC GENMOD. Corresponding overall intra cluster correlation (ICC) coefficient was also estimated from GEE method using the CORRW option from the SAS PROC GENMOD.

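### Entry to the analysis depends on timely recording of weight and height, which the intervention changes in one arm only: a built-in selection risk of unknown size and sign

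*Protocol article*

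**What the plan says.** All references are to the protocol article.

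- **Entry of children (Participants, Table 1).** The inclusion criterion is "Children recorded as malnourished based on their weight/height and height/age ratios upon hospital entrance". The exclusion is "First weight recorded more than 2 days after admission, first height recorded more than 15 days after admission". The text below the table says that nutritional status is assessed "based on weight and height measured at admission by health care workers", that is, by ward staff and not by the research team.
- **What the intervention does to recording.** Under Awareness campaign, the message to nurses is to weigh and measure systematically. Under Leadership based strategy, the hospital's boards "established the mandatory measurement of the weight and height of each hospitalised child" and required entry in the IT system, with department heads and nursing coordinators ensuring compliance. The declared purpose is: "A leadership oriented strategy focused mainly on increasing the sensitivity of the computerised malnutrition screening system".
- **Control arm (The control group).** Usual care, with no screening system and with "no educational campaign and no leadership based strategy".
- **Timing (Time frame).** Clusters were randomised in February 2010 and trial data run from March 2010. The campaign and the leadership strategy are placed in the intervention clusters. Under Blinding, nobody was blinded.
- **Analysis set (Data analysis).** "All malnourished children screened in all clusters allocated to the intervention or control arm will be included in the analysis". Adjustment is for age, severity of malnutrition, comorbidities, complications and length of stay.

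**The concern.** In a cluster trial, randomising wards protects the comparison only if children enter the analysis in the same way in both arms. Here entry is settled after randomisation by a staff behaviour that the intervention is designed to change. If it works as intended, intervention wards will record weight and height for some malnourished children whom control wards would have left unmeasured or measured late. Those children enter one arm's denominator and not the other's.

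All three primary outcomes (weighings per day of stay, investigation of etiology, management by a dietician or the NST) are computed among the children captured. If the extra children differ in the care they would have received anyway, the arms differ before any effect on care. The before-and-after comparison within the intervention arm has the same weakness, because recording may change at the start of the intervention.

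The weighing outcome is the sharpest case. A child first weighed after day 2 is excluded, although a late first weighing is itself the kind of poor adherence that this outcome should register.

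**Working it through.** **The plan's own figure.** The sample size section gives 1289 children for 50% against 75%, two-sided alpha 0.05, power 80%, ICC 0.05 and cluster size 200. Design effect: 1 + (200 − 1) × 0.05 = 10.95. With the mean proportion 0.625 in both variance terms, n per arm = (1.96 + 0.84)² × 2 × 0.625 × 0.375 / 0.25² = 58.87 (unrounded normal quantiles). Total: 2 × 58.87 × 10.95 = 1289.2. The stated number reproduces, and this point does not depend on it. It supplies only the yardstick of 25 points.

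**Is entry dependent on arm?**

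1. Entry needs a first weight within 2 days, a first height within 15 days and a classification as malnourished. For stays shorter than 15 days, the height condition amounts to whether a height was recorded at all.
2. Ward staff generate these records after allocation, unblinded.
3. Training, enforcement and alerts that bear on recording are confined to intervention clusters.
4. The intention-to-treat set is defined as the screened malnourished children, so the denominator itself can vary with arm.
5. Covariate adjustment works among captured children. It cannot restore children who were never recorded.

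The article describes no arm-independent measurement of weight and height, and no analysis whose denominator is free of recording.

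**Illustration for a binary outcome.** The article gives no recording rates, so every input here is an assumption. Let c and i be the shares of malnourished children meeting the entry rule in control and intervention, with c < i. Assume that every child captured under usual care would also be captured under the intervention. Let d be the amount by which care is less frequent in the extra children. With no true effect:

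apparent difference = −d × (i − c) / i

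| c | i | d = 10 points | d = 20 | d = 30 |
|---|---|---|---|---|
| 90% | 95% | −0.5 | −1.1 | −1.6 |
| 80% | 90% | −1.1 | −2.2 | −3.3 |
| 70% | 90% | −2.2 | −4.4 | −6.7 |
| 50% | 90% | −4.4 | −8.9 | −13.3 |

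For example, c = 70%, i = 90%, d = 20 gives −20 × 0.20 / 0.90 = −4.4. A true gain of 25 points in all children would appear as 25 − 0.5 = 24.5 at one end and 25 − 13.3 = 11.7 at the other. If d is negative (the extra children receive more care), every sign reverses. If c = i and the same children are captured, the bias is zero.

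**Would a composite per eligible stay repair it?** Consider counting children who are both recorded as malnourished and managed. Take a true management rate of 50% in both arms, 60% among measured control children, and i = 90%.

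- c = 60%: the rate in the unmeasured is (0.50 − 0.6 × 0.60) / 0.4 = 0.35. Control scores 0.6 × 0.60 = 0.36; intervention scores 0.36 + 0.3 × 0.35 = 0.465. Difference: +10.5 points.
- c = 70%: the rate in the unmeasured is (0.50 − 0.42) / 0.3 = 0.267. Control scores 0.42; intervention scores 0.42 + 0.2 × 0.267 = 0.473. Difference: +5.3 points.

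Both arise with no difference in management, because the composite credits recording itself.

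**The case against.** **No difference in capture is shown.** A reader might infer that the two arms do analyse differently selected children. The article does not show that. It says the score was applied to every child, the height window is lenient, and no rates by arm are given. This stands: the point is a risk built into the rules, not an observed difference.

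**The direction is not documented.** It is tempting to suppose that children measured under usual care were already under nutritional attention, so that control adherence is inflated and the bias runs towards no benefit. Nothing in the article says so, and the opposite sign is possible.

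**Large biases need large hidden gaps.** Fixing the overall rate at 50% and assuming 70% care among measured controls gives −14.8 points at c = 70% and i = 90%. But it implies (0.50 − 0.49) / 0.30 = 3.3% care in the unmeasured, a gap of about 67 points. Such a figure is an extreme bound and should not be set against 25 points as if typical.

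**Contamination of controls.** The Leadership section, read alone, could mean a hospital-wide mandate that reached control wards. The control group section and the Time frame section both place the leadership strategy in the intervention arm, so this is loose wording and not a demonstrated contamination. A hospital-wide rule would also shrink the recording difference, though training, enforcement and alerts would still differ.

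**Detection is a different question.** The stated aim is adherence to recommended care in malnourished children, so leaving detection out of the primary outcomes is a legitimate choice. Reporting of patient flow is commonly left to a fuller plan. That also stands, but the eligibility rule and the analysis set are fixed in this article, and the risk follows from them.

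**Conclusion.** The concern holds as a selection risk of unknown size and sign. Entry is decided after randomisation through a behaviour that the intervention trains and enforces in one arm only, and neither intention-to-treat by cluster nor the planned adjustment removes it. It affects the between-arm comparison and the before-and-after comparison in the intervention arm, and it is sharpest for the weighing outcome.

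The range of about −0.5 to −13 points under a true null rests wholly on the assumed capture rates and care gaps, and on the extra children receiving less care. It shows that the bias could be negligible or could take up to about half of the planned 25 points. It does not show which. Without capture rates by arm, an attenuated or an enhanced result could not be interpreted with confidence.

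**What to change.** 1. Among all stays in the participating units that meet the age and length-of-stay criteria, report the share with timely weight and height by arm, cluster and period, including the six-month baseline phase. Compare the characteristics of captured children between arms.
2. Add a sensitivity analysis of the primary outcomes weighted by the inverse probability of timely measurement, using the admission variables available. State that it cannot remove selection on nutritional concern that was never recorded.
3. Add a sensitivity analysis that keeps children who can be classified but whose first weight or height was late. This matters most for the weighing outcome.
4. If capture differs between arms, limit the conclusion accordingly.
5. Do not use the composite of recorded as malnourished and managed as a key analysis of management. At most, report it as a separate outcome for detection plus care.
6. Reword the Leadership section so that it agrees with the control group and Time frame sections on where the mandate applied.

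Cost: some data linkage and analysis, and added variance from the weights. The article says the claims databases supplied length of stay and cost. It does not say that they hold dates of weight and height, so those may have to come from the IT system or the medical records. The article describes the statistical work as still in progress, so these analyses can be added.

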### Outcomes and measurements

Primary outcomes were chosen for their ability to assess the quality of care within each cluster based on health care workers’ adherence to recommended practices for every malnourished child; they included the number of daily weighings during hospitalisation (total number of weighings divided by length of stay), the investigation of malnutrition etiology (a detailed analysis of malnutrition causes is present in the medical record) and the management of malnutrition by a dietician and/or the NST.

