#### Secondary outcome measures

*For clinical practice*: Appropriate call-in of the NST;

*For clinical impact on children*:

Incidence of complications linked to nutritional status during the hospital stay;

Evolution of nutritional status during the hospital stay;

*For economic measures*: Mean length and cost of stay.

Data concerning primary and secondary outcome measures were available at the patient level and were extracted from the medical records by an independent research team. The research team received handouts and training to become familiar with data collection. Data relative to the length of stay and the cost of treatment were obtained from the hospital’s claims databases.

The same data were gathered for the observational study and for the interventional study.

In addition, we monitored the intervention process. The research team gathered information on the availability and usage of the information technology tools, on the actions carried out by the NST in the framework of the awareness campaign for health care workers, and on the actions conducted within the leadership based strategy.

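### Excluding stays under 2 days selects children on a post-allocation variable that is itself an outcome, so length and cost of stay may be truncated differently by arm

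*Protocol article*

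**What the plan says.** In the protocol article, Table 1 (Participants, patient level) lists "Stay less than 2 days" among the exclusions. It does not mention expected or planned stay.

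Under Secondary outcome measures the economic outcome is "Mean length and cost of stay", and "Data relative to the length of stay and the cost of treatment were obtained from the hospital’s claims databases". Length of stay also has three other uses:

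- It is the denominator of the weighing primary ("total number of weighings divided by length of stay").
- It is the offset of that primary's model ("For the GEE Poisson, the length of stay will be used as an offset").
- It is an adjustment covariate ("complications occurrence and length of hospital stay").

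Time frame puts randomisation of the six clusters in February 2010 and trial data collection from March 2010 to August 2011. The analysis section describes the analysis set thus: "All malnourished children screened in all clusters allocated to the intervention or control arm will be included in the analysis". The article describes no length or cost analysis that retains short stays, and no comparison of the excluded share between arms.

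**The concern.** A stay is known only at discharge. For every trial-phase child that comes after cluster allocation and, in the intervention arm, potentially after the alert and the dietician or NST contact. The rule therefore decides who is analysed by the value of something the intervention may change and the trial sets out to measure.

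The article gives reasons why stay could move either way. The Background expects nutrition teams to reduce complications and save money. The nutritional support policy adds an aetiology work-up and daily weighing, and nutritional support in severe cases, any of which could lengthen a stay. A stay shortened to under 2 days leaves the comparison instead of counting as a saving, and a stay lengthened past 2 days enters it. Either shift makes the two analysed groups differ in composition. What is at stake is mainly the economic comparison and, to a lesser degree, the process primaries.

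**Working it through.** **The plan's own figure, for scale.** Inputs from the sample size section: 50% v 75%, two-sided alpha 0.05, power 80%, ICC 0.05, cluster size 200.

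- n per arm = 2 × 0.625 × 0.375 × (1.960 + 0.842)² / 0.25² = 58.87
- design effect = 1 + 199 × 0.05 = 10.95
- N = 2 × 58.87 × 10.95 = 1289.2, against the stated 1289

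The figure reproduces and is unaffected by this point. It fixes the planned effect at 25 percentage points.

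**Length of stay, uniform shortening.** The documents give no stay distribution, so what follows is assumed. Take log-normal stays with log-median μ and log-SD s, cut at 2 days:

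- share excluded = Φ((ln 2 − μ)/s)
- mean of the retained = exp(μ + s²/2) × Φ((μ + s² − ln 2)/s) / (1 − share excluded)

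With control median 4 days, s = 0.9, and every stay shortened by 20% (median 3.2):

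| | Control | Intervention | Reduction |
|---|---|---|---|
| Share excluded | 22.1% | 30.1% | |
| Mean, all stays (days) | 6.00 | 4.80 | 1.20 days, 20% |
| Mean, stays of 2 days or more | 7.33 | 6.33 | 1.00 day, 13.6% |

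Over medians 3, 4, 5 and s = 0.7, 0.9, 1.1 the analysed reduction runs from 11.8% to 15.8%.

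**Other shapes.** The control mean was set at 3, 5 or 8 days, with stays exponential or log-normal (CV 0.8 to 1.5).

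- A true mean ratio of 0.80 appears as 0.83 to 0.91, and the excluded shares differ between arms by about 4 to 13 points.
- A true ratio of 0.90 appears as 0.91 to 0.95, and 1.10 as 1.05 to 1.09.
- The difference in days shrinks by 8 to 31% under the log-normal and by 0% under the exponential.

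**Shortening confined to longer stays.** Same log-normal (median 4, s = 0.9), 20% shortening only from a threshold upward. The shortest affected stay becomes 0.8 × 2.5 = 2.0 days or more, so nobody crosses the line and 22.1% are excluded in both arms.

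| Shortening from | True reduction, all stays | Analysed reduction |
|---|---|---|
| 2.5 days | 18.4% (1.11 days) | 19.4% (1.42 days) |
| 3 days | 17.8% (1.07 days) | 18.7% (1.37 days) |
| 4 days | 16.3% (0.98 days) | 17.1% (1.26 days) |

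There is no attenuation. The analysed reduction is slightly larger because the unaffected short stays are left out of both arms.

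**Process primaries, no true effect assumed.** Two mechanisms were tried.

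- *Lengthening.* Let a net excess e of intervention children, all with the outcome met, be brought into the sample. The rate becomes (0.5 + e)/(1 + e): 51.0%, 52.4% or 54.5% for e = 2%, 5% or 10%.
- *Shortening.* Let 2%, 5% or 10% of the retained control children be of a kind that would fall below 2 days under the intervention, with process rates 20 to 45 points lower. The spurious difference is the product of the two: 0.4 to 0.9, 1.0 to 2.3 or 2.0 to 4.5 points.

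At most this is 4.5 points against the planned 25.

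**The case against.** The strongest reply is that the attenuation follows from the assumed effect shape. Nothing in the article says that a dietician contact or a work-up brings a stay of just over 2 days below 2, and if only longer stays respond the bias vanishes. This stands: the problem is conditional, not established.

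A minimum stay also has a rationale. Repeated weighing, an aetiology work-up and a dietician or NST visit need time in hospital. That justifies the rule for the process primaries but gives no reason to truncate length and cost.

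Nor is dropping the rule outright clean. Classing a child as malnourished needs a recorded weight and height. Mandatory measurement and entry belonged to the leadership strategy, which the control arm did not receive, and Table 1 tolerates a first height up to 15 days after admission. Short-stay control children may therefore be the likeliest to go unclassified, so adding short stays could lower the intervention mean through ascertainment alone. This stands and shapes the fix.

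Two stronger readings are tempting, and the article supports neither:

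- A reader might infer that only intervention stays can be prolonged past 2 days. The control group section says that usual care continued and that the NST could be called at any time, so only a net difference between arms matters.
- A reader might infer that the rule contradicts the intention-to-treat statement. That sentence reads naturally as all eligible children, analysed as their cluster was allocated. Read literally, it would conflict with every patient-level exclusion in Table 1.

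**Conclusion.** The concern holds in a conditional form. Eligibility depends on a post-allocation variable that is also a secondary outcome, and nothing in the article offsets this. Taking the stay as realised is the natural reading of the table, not its stated wording.

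If stays near 2 days respond to the intervention, the ratio of mean stays moves toward 1: a uniform 20% reduction would be seen as about 12 to 16% under the log-normal grid. If only longer stays respond, there is no attenuation. The documents give no data to choose between these cases, so the size is unknown. The same selection applies to cost of stay, for which no figure was computed. For the process primaries the bias is likely small against 25 points and does not call the 2-day rule into question. The point is worth acting on for the economic outcomes and as a sensitivity check elsewhere.

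**What to change.** 1. For length and cost of stay, add an analysis of all children classed as malnourished on their admission measurements, whatever their stay, beside the analysis restricted to 2 days or more.
2. Report by arm and by period (observational and trial phases) the share excluded for short stay, and the share of short stays with both weight and height recorded. If recording differs between arms, read the added analysis with that in mind.
3. Keep the 2-day rule for the three primaries, and repeat the aetiology and dietician/NST analyses with shorter stays included as a sensitivity analysis.

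The cost is a wider extract from the claims databases, linked to the admission measurements, and some extra chart reading for two yes/no items. The Time frame section says that the data were still being analysed, so no trial conduct would change. The remaining weakness is that short stays may be ascertained unequally between arms, which item 2 makes visible but does not remove.
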